### Aim of the trial

The YOURTREAT trial is part of the study consortium “Stress, Health and Integration of Young Refugees: Discovering the Interrelations and Improving Access to Healthcare (YOURHEALTH)” funded by the German Federal Ministry of Education and Research (Bundesministerium für Bildung und Forschung; BMBF). This funding agency had no influence on the trial design and will not influence data collection, data management, data analyses, interpretation of study results, publication nor report writing. Within this consortium, the clinical trial YOURTREAT aims to test whether the treatment of young refugees (10–18 years) with KIDNET causes an effective reduction of PTSD and comorbid symptoms. In more detail, KIDNET will be implemented within an innovative complementary health care system that is attached to outpatient clinics of universities and university hospitals. The treatment in the outpatient clinics will be supported by Intercultural Therapy Assistants (ITAs) who will interpret the diagnostic interviews and therapy sessions if required, but can also further support the therapeutic process by accompanying young refugees on their way to and from the therapy, or support the recruitment and eligibility screening into the study. The treatment with 11 sessions of KIDNET supported by ITAs will be compared to treatment as usual (TAU) for young refugees within the general health care system in Germany.

The primary hypothesis of this trial is that, 6 and 12 months after randomization, children who received KIDNET compared to children referred to the regular health care system in the TAU condition will show a greater PTSD symptom reduction. The secondary hypothesis refers to a superiority of KIDNET for the reduction of comorbid depressive, internalizing and externalizing symptoms, as well as suicidal ideation and a reduction of strain caused by discrimination, as well as an improvement of physical health. Furthermore, a lower rate of individuals who still meet the diagnostic criteria of PTSD and a greater response rate is expected in the KIDNET group as opposed to the TAU group.

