## Methods

### Trial design

YOURTREAT is a randomized controlled, rater-blinded, two-arm, multi-center, superiority trial with a 1:1 allocation ratio to two parallel groups. Individuals who are screened eligible for the trial will participate in a comprehensive diagnostic interview (t_1_). Among other information (detailed below), this structured interview will assess the diagnosis of PTSD according to the *Diagnostic and Statistical Manual of Mental Disorders, 5th edition* (*DSM-5*). We expect that we will have to interview approximately *N* = 220 children and adolescents (*N* = 55 per site) in order to identify 80 participants (*N* = 20 per site) who fulfill the diagnostic criteria of PTSD. These PTSD patients will be immediately randomized to one of the two arms of the trial; KIDNET or TAU. For individuals included in the KIDNET group, the treatment starts within 1 month after the diagnostic interview and should be terminated at the latest 5 months after randomization. For the beginning and ending of the NET, a tolerance window of 1 week is considered acceptable. Deviations from this time window will be reported. Individuals assigned to TAU will be informed about treatment and counseling options within the local general health care system immediately after the diagnostic interview.

Six months after the diagnostic interview and the randomized group allocation, the first follow-up interview will take place (t_2_). This time point was selected in order to assure a minimum time interval of 1 month between the end of KIDNET and the first follow-up interview. In this way, the diagnostic interview which measures PTSD symptoms in the past month, will not be biased by the experience of symptoms during exposure therapy. The second follow-up interview (t_3_) is scheduled for 12 months after randomization. For the appointments of the follow-up interviews, a tolerance window of ±  2 weeks is considered acceptable. Deviations from this time window will be reported. See Fig. 1 for a schematic overview of the participant flow through the trial. The study protocol was written following the Standard Protocol Items: Recommendations for Interventional Trials (SPIRIT) Statement 2013 [32]. See Additional file 1 for the SPIRIT Checklist. The trial was registered at the German Clinical Trials Registry (Deutsches Register Klinischer Studien; DRKS) on 15 May 2019 (ID: DRKS00017222).

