## Statistics

### Power analysis and sample size calculation

The Ruf et al. pilot study [26] achieved a treatment effect size of 1.9 for NET and 0.3 for the waiting-list control group. However, we expect that the contrast will be smaller for this study, as we will have an active control condition and will provide detailed information to children and adolescents from the TAU condition on how to seek treatment in the regular health care system. Therefore, we base the effect size calculation at a conservative estimation of a between-group effect size of *d* = 0.6. To test the hypothesis that a treatment with KIDNET is more effective than TAU, with a one-sided alpha level set at 0.05 and a power level of 0.8, we need to enroll *N* = 72 subjects (*N* = 36 per group) into the present study. Once randomized, loss to follow-up was small (generally lower than 5%) in the Ruf et al. study [26] as well as in other NET studies [50]. Most importantly, as the main analysis of the primary outcome measure will be calculated using a mixed-effects model, all randomized cases can be included in the statistical analyses. Therefore, the intended sample size of *N* = 80 will be sound to answer the research questions of the trial.

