### Data analyses

The confirmatory analysis of this study will be calculated as a mixed-effects model with the CAPS-CA-5 score as the outcome variable. Mixed models are especially suited for longitudinal studies as they can account for serial correlation within participants, are relatively robust to randomly missing data, and can incorporate certain nonrandom missing data without biasing model estimates. In detail, participants will be modeled as a random factor (including random intercepts or random intercepts and slopes), while time and intervention (KIDNET vs. TAU), as well their interaction, will be modeled as fixed factors. The hypothesis that KIDNET is superior to TAU in the treatment of PTSD will be evaluated by the significance test of the interaction effect time × intervention.

In case of a significant interaction effect, two planned general linear hypotheses will be calculated as post-hoc tests for linear mixed-effect models in order to test between-group differences at t_2_ and t_3_. One-sided *p* values will be adjusted for multiple comparisons following the Holm procedure.

We will perform an intention-to-treat analysis; that is, all trial participants will be analyzed as randomized, even if they discontinue treatment or are unavailable for one or both of the follow-up interviews. The between-group effect size (Cohen’s *d*) will be calculated at each follow-up assessment (t_2_ and t_3_). The intention-to-treat analysis will be supplemented by a modified intention-to-treat analysis which will include only those participants who participated in at least one post-randomization diagnostic interview. Furthermore, participants who were randomized to KIDNET will be included only if they participated in at least one KIDNET therapy session.

Continuous secondary outcome measures are analyzed in the same way. In the absence of a valid cut-off score for clinically significant change or treatment response of the CAPS-CA-5, the rate of subjects with clinically significant improvement as well as worsening based on the RCI will be compared between groups using Fisher’s exact tests at the follow-up assessments t_2_ and t_3_, separately. For this purpose, the RCI will be calculated based on the pre-treatment scores of the study sample following the suggestion of Jacobson and Truax [39]. Missing values due to premature withdraw will be considered as treatment failure (classified as no response).

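### The Holm adjustment of the 6- and 12-month contrasts is valid but needlessly conservative behind the interaction gate; what it costs depends on the claim, the contrast and an unstated visit correlation

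*Protocol article*

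**What the plan says.** The Data analyses section of the protocol article evaluates superiority by the time × intervention term of a mixed model for the CAPS-CA-5 score. Only if that term is significant are two planned contrasts tested, one for the group difference at t2 and one at t3, described as post-hoc tests. Their one-sided p "values will be adjusted for multiple comparisons following the Holm procedure". The same section sets 0.05 as the significance level for all analyses and applies the same approach to the continuous secondary outcomes.

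The Aim of the trial section words the primary hypothesis for both time points: "6 and 12 months after randomization, children who received KIDNET compared to children referred to the regular health care system" are expected to show the greater symptom reduction.

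The sample size section rests on "a conservative estimation of a between-group effect size of" d = 0.6, "with a one-sided alpha level set at 0.05 and a power level of 0.8", which leads to 72 "subjects (*N* = 36 per group) into the present study". It concludes that "the intended sample size of *N* = 80 will be sound to answer the research questions" of the trial. Trial design describes a "superiority trial with a 1:1 allocation ratio to two parallel groups", so 80 means 40 per arm.

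**The concern.** The plan controls multiplicity over the two visits twice. The interaction test already tests the joint hypothesis of no difference at either visit. Once it rejects, closed testing lets each of the two remaining hypotheses be tested at the full level. If the claim instead needs both visits, no adjustment is needed either, because both tests must succeed.

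What is at stake is power for the visit-level statements: whether KIDNET is better at 6 months, at 12 months, or at both. In an 80-patient trial in a population that is hard to recruit and retain, power that can be recovered without loosening the 5% limit is worth having. The same rule also governs every continuous secondary outcome.

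**Working it through.** **1. The plan's own figure.** For d = 0.6, one-sided 0.05 and power 0.80, the exact noncentral t gives power 0.7996 with 35 per arm and 0.8095 with 36. The first size that reaches 80% is 36 per arm, N = 72, as stated. This is the power of one ungated, unadjusted two-group comparison.

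**2. Why the gate suffices.** Call the hypotheses H2 (no benefit at t2) and H3 (no benefit at t3). Randomization makes the true baseline difference zero, so no difference at t2 and t3 implies no interaction. The gate is then a 0.05 test of H2 and H3 jointly. With two hypotheses that is the only intersection, so testing H2 and H3 each at 0.05 after the gate completes a closed procedure.

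One detail needs checking. The gate is two-sided while the contrasts are one-sided, so harmful effects must be covered as well. Simulation did this (40 per arm, 2-df gate). Familywise error in %, shown as without Holm / with Holm:

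| True effects | r = 0.2 | r = 0.5 | r = 0.8 |
|---|---|---|---|
| 0 at both visits | 1.81 / 1.25 | 1.24 / 0.79 | 0.76 / 0.46 |
| t2 benefit 1.0, t3 zero | 4.50 / 4.50 | 4.98 / 4.98 | 5.05 / 5.05 |
| t2 harm 0.6, t3 zero | 4.60 / 2.38 | 4.75 / 2.40 | 4.99 / 2.51 |
| t2 harm 1.0, t3 zero | 5.00 / 2.52 | 5.00 / 2.49 | 4.99 / 2.48 |

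Over wider grids of null and harmful effects the largest estimate without Holm was 5.2%, which is consistent with 5% for a maximum of many noisy estimates. With neither gate nor Holm, the error with no effect at either visit is 9.48%, 8.79% and 7.51% at r = 0.2, 0.5 and 0.8. The gate therefore supplies the control.

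**3. Where the power goes.** With SD 1 and 40 per arm, the standard error of a raw group difference is √(2/40) = 0.2236, so d = 0.6 gives 0.6/0.2236 = 2.683. Ignoring the gate, power at one-sided 0.05 is Φ(2.683 − 1.645) = 85.0%, and at Holm's first step of 0.025 it is Φ(2.683 − 1.960) = 76.5%.

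The gate limits how much of that gap can be recovered. Under equal correlation r between all visits and d = 0.6 at both, its noncentrality is n·d²/[3(1 − r)] = 40 × 0.36/[3(1 − r)] = 4.8/(1 − r). That is 6.86, 9.6 and 16 at r = 0.3, 0.5 and 0.7. The 2-df chi-square power at 0.05 is then 64.6%, 79.9% and 95.7%. At low r the gate is the bottleneck and Holm matters little; at high r the gate nearly always passes and Holm bites.

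**4. Cost of Holm, raw contrasts at t2 and t3.** Power in %, with Holm → without; r is assumed, normal approximation.

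| Claim | r = 0.3 | r = 0.5 | r = 0.7 |
|---|---|---|---|
| A given visit, d = 0.6 at both | 56.3 → 57.2 | 67.6 → 69.6 | 78.4 → 81.8 |
| At least one visit, d = 0.6 at both | loss 1.6 | 73.4 → 76.7 | 83.0 → 88.6 (loss up to 5.7 in a repeat run) |
| t3, effects 0.3 and 0.6 | loss 1.9 | 57.3 → 61.1 | 70.5 → 77.2 |
| Both visits, d = 0.6 at both | 50.7 → 51.1 | 61.7 → 62.4 | 73.8 → 75.1 |

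For both visits with effects 0.3 and 0.6 the loss is about 0.3 points. Using t-based tests and a Hotelling gate instead lowers the levels slightly but leaves the losses alike: at least one visit goes from 71.5% to 74.8% at r = 0.5 and from 82.2% to 88.0% at r = 0.7.

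**5. Cost if the contrasts are differences in change from t1.** With the 2-df gate the loss is 0.03 points or less for equal effects and at most about 0.6 for unequal effects. With time entered linearly it is zero.

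**The case against.** The strongest case against is that nothing here is wrong. Holm is prespecified, valid and clearly stated, and it protects the visit-level claims even if the gate is later dropped or fails to hold its level. All of that stands.

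Four stronger readings are tempting, and the protocol does not support them.

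- A reader might infer that the trial loses power for its main decision, or that children are enrolled for power that is thrown away. The Data analyses section settles superiority by the interaction test, and Holm does not touch that test.
- A reader might take a loss of 2 to 7 points as general. It needs raw contrasts, a correlation of about 0.4 or more, and either an at-least-one-visit claim or unequal effects. The primary hypothesis names 6 and 12 months; read as needing both, the loss is about 0.3 to 1.3 points. The primary outcome is defined as change from t1, and if the contrasts are coded that way the loss nearly vanishes. The wording of the contrasts, as between-group differences at t2 and t3, favours the raw reading, but the article does not fix the coding.
- A reader might blame Holm for the very low error rate when there is no effect at either visit. That comes mostly from the gate: at r = 0.5 it is 0.79% with Holm and 1.24% without. When one visit has a large benefit and the other none, Holm already uses the full 5%.
- A reader might say that Holm brings no error benefit at all. It brings none against the 5% limit, but it does lower the actual error in places, for example from 5.00% to 2.49% with a harm of 1.0 at t2, no effect at t3 and r = 0.5.

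**Conclusion.** The point holds as a minor, optional improvement to an explicitly stated rule. Given the gate, exactly two hypotheses and a zero true baseline difference, the Holm step is not needed to keep familywise error at 5%.

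The size depends on what is claimed and on a correlation that the protocol does not report. Across an assumed 0.3 to 0.7 with 40 per arm and raw contrasts, the range runs from about 0.3 points (both visits) to about 7 points (t3 alone under unequal effects). It falls to between 0 and 0.6 points if the contrasts are differences in change. The figures assume complete data, a common SD and equal correlation between visits; the protocol expects little dropout, noting that in earlier studies "loss to follow-up was small (generally lower than 5"%. They also assume that the interaction test holds its 0.05 level.

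**What to change.** Replace the Holm sentence with: *After a significant time × intervention test, the differences at t2 and t3 are each tested at one-sided 0.05; with two hypotheses this closed procedure controls the familywise error at 5%.* Add that Holm applies only if the interaction gate is removed. The continuous secondary outcomes follow automatically, since they are analysed in the same way.

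The cost is one sentence, with no change to patients, visits or data. The small downside is that the actual error rate rises in some configurations while staying within 5%. The change is safe only while the gate is kept, and it should be made before any comparative outcome data are seen.

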#### Treatment as usual (TAU)

Children and adolescents allocated to the TAU group will be referred to the local regular health care system for treatment. Immediately after the communication of group allocation, they will receive detailed information on how to find psychotherapeutic support in their community. For children under the age of 16 years, the psychoeducation on how to find psychotherapeutic support in the community will take place in the presence of the parent or guardian. The interventions provided to the TAU group will be assessed after each follow-up diagnostic assessment.

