#### Blinding

Due to the behavioral nature of the intervention, neither participants nor therapists and ITAs who interpret the therapy can be blinded. However, the group allocation of the subjects will be concealed from the independent outcome assessors who will conduct the follow-up interviews. At the beginning of the follow-up interviews, participants will be instructed not to reveal any information related to the group that they have been assigned to or regarding the therapeutic process. After the completion of all diagnostic instruments of the follow-up interview, the independent assessors will complete a questionnaire asking whether any information regarding group allocation was revealed in the diagnostic interview. Cases of premature unblinding will be documented and reported.

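### The supplementary modified ITT set drops KIDNET participants who attended no session but has no matching rule in TAU, so it is not a randomised comparison and is likely, though not certain, to favour KIDNET

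*Protocol article*

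**What the plan says.** Under Data analyses, the protocol article makes the main analysis a full ITT analysis: "all trial participants will be analyzed as randomized, even if they discontinue treatment or are unavailable for one or both of the follow-up interviews". It then adds: "The intention-to-treat analysis will be supplemented by a modified intention-to-treat analysis". Two rules define that second set.

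- Both arms: it "will include only those participants who participated in at least one post-randomization diagnostic interview".
- KIDNET only: "participants who were randomized to KIDNET will be included only if they participated in at least one KIDNET therapy session".

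No sentence asks a TAU participant to have taken up any care. The section Treatment as usual (TAU) describes that arm as a referral: its members "will be referred to the local regular health care system for treatment". Uptake is nevertheless recorded: "The interventions provided to the TAU group will be assessed after each follow-up diagnostic assessment". Under Blinding, the article states that "neither participants nor therapists and ITAs who interpret the therapy can be blinded". Under Trial design, KIDNET may begin up to a month after the diagnostic interview, so there is an interval in which a child who knows the allocation may fail to start. The article gives no expected never-start rate and no reason for the one-arm rule.

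**The concern.** Children who would not start KIDNET if offered it are present in both arms by randomisation. The session rule removes them from KIDNET, where they can be seen, and leaves their counterparts in TAU, where they cannot. The same holds for care received: a KIDNET child who received no treatment leaves the set, while a TAU child who received none stays.

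Non-starting is unlikely to be random. The article's Discussion names unstable mood and motivation, and unstable housing, as reasons why this population drops out of trials. If non-starters would have fared worse anyway, removing them from one arm flatters KIDNET.

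The modified set is the only alternative analysis set that Data analyses names. Readers will probably take agreement between it and the ITT result as reassurance, which a set built this way cannot give.

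**Working it through.** **The plan's own figure.** Power analysis and sample size calculation gives d = 0.6, one-sided alpha 0.05, power 0.8 and N = 72. The normal formula gives 2 × (1.645 + 0.842)² / 0.6² = 34.3, so 35 per arm. The one-sided t-test gives 35.04, so 36 per arm and N = 72. The figure reproduces, and the session rule does not touch it.

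**Model.** Outcomes are in SD units, with benefit positive.

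- p: share of each arm who would not start KIDNET but do attend a follow-up interview. Never-starters with no follow-up are already removed by the common rule and do not count.
- g: how much worse their prognosis is than that of starters, without KIDNET.
- c: effect of KIDNET in starters, with no effect in never-starters.

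The article gives neither p nor g, so the values below are assumptions. Its loss to follow-up, generally under 5% in earlier studies, is not a never-start rate.

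**Formulas.**

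- TAU mean: −p × g. KIDNET mean after exclusion: c.
- Modified ITT difference: c + p × g.
- ITT difference: (1 − p) × c.
- Bias relative to the effect in starters: (c + p × g) − c = p × g.
- Excess over ITT: p × (c + g).

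To hold the ITT effect at the planned 0.6, set c = 0.6 / (1 − p). For the case of no true effect, set c = 0 and use a normal approximation with 40 × (1 − p) KIDNET and 40 TAU patients: SE = √[1/(40(1 − p)) + (1 + p(1 − p)g²)/40] and alpha = Φ(p × g / SE − 1.645).

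| p | Children in an arm of 40 | Bias p × g, g = 0.5 | Set reads, ITT = 0.6, g = 0 | Set reads, ITT = 0.6, g = 0.5 | One-sided alpha, c = 0, g = 0.5 |
|---|---|---|---|---|---|
| 2.5% | 1 | 0.0125 | 0.615 | 0.628 | 0.056 |
| 5% | 2 | 0.025 | 0.632 | 0.657 | 0.062 |
| 10% | 4 | 0.05 | 0.667 | 0.717 | 0.077 |
| 20% | 8 | 0.10 | 0.750 | 0.850 | 0.110 |

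Worked row, p = 10%: c = 0.6 / 0.9 = 0.667. With g = 0.5 the set reads 0.667 + 0.05 = 0.717. With c = 0, SE = 0.231, 0.05 / 0.231 = 0.216, and Φ(0.216 − 1.645) = 0.077.

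**Direction.** At an ITT effect of 0.6, the set falls below ITT only if never-starters would do better than starters by more than c, which is 0.63 SD at p = 5% and 0.75 SD at p = 20%. With no true effect the sign depends on g alone. If never-starters do 0.5 SD better, alpha falls to 0.040 at p = 5% and 0.031 at p = 10%.

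**Two separate quantities.** The g = 0 column is not bias. It is the effect in starters, which ITT dilutes. Only the further step from g = 0 to g = 0.5 is prognostic bias.

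**The case against.** No confirmatory conclusion rests on this set. The ITT analysis of everyone randomised is primary, the exclusion rule is published beside it, and the article never states that the set is meant to test the robustness of the ITT result. A reader might infer that the trial's main result is biased. It is not: the confirmatory test, the Holm-adjusted comparisons and the sample size are all untouched. This part of the objection stands and limits the weight of the point.

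A reader might also multiply the share of never-starters by their whole outcome gap from treated starters. With 10–20% never-starters and a gap of 0.5–1.0 SD, that gives 0.05–0.20 SD, or 8–33% of d = 0.6, and all of it might be called bias. The article does not support this. It offers no basis for 10–20%. The gap also contains the treatment effect that starters received: if 0.6 of a gap of 1.0 is treatment effect, the prognostic part at 20% is 0.2 × 0.4 = 0.08 SD, not 0.20. Moreover, children who relocate will often miss follow-up too, and the common rule already removes them from either arm.

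The missing TAU counterpart also partly reflects the comparator. TAU is referral and information given straight after allocation, so a rule of having received the assigned condition would be met by nearly everyone in that arm. This explains the asymmetry but does not cure it, because the children who would not have started KIDNET still remain in TAU.

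**Conclusion.** The defect is real and is stated in the text; it is not a detail left for an analysis plan. The modified set conditions on starting therapy, after an unblinded allocation, in one arm only. It is therefore not a randomised comparison.

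A tilt towards KIDNET is the likely direction. It is not certain, because the article says nothing about the prognosis of never-starters. With g = 0.5 the bias relative to the effect in starters runs from 0.0125 SD (one child in 40) to 0.10 SD (eight in 40). With no true effect, one-sided alpha rises from 0.05 to about 0.06 at p = 5% and 0.08 at p = 10%. At a low never-start rate the distortion is small.

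Apart from bias, the set answers a different question. Unless never-starters have a markedly better prognosis, it will read above ITT whenever KIDNET works. Agreement between the two, or a larger effect in the modified set, therefore says nothing about the robustness of the ITT result.

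**What to change.** Delete the KIDNET-only session criterion, so that the modified set is every randomised participant with at least one follow-up interview, under the same rule in both arms. Report exclusions by arm with reasons. Adding a care-uptake rule in TAU would not help: children who take up KIDNET and children who take up regular care need not be alike.

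If the effect of actually starting KIDNET is wanted, replace the subset with a complier-average estimate. Use randomisation as the instrument, count at least one session as received, and adjust for t1 CAPS-CA-5 and center.

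Costs:

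- The text change is one sentence.
- The symmetric set will be close to ITT, since it drops only participants without follow-up data and so adds little. Selection through follow-up attendance can remain in it.
- The complier-average estimate has a wider interval than the subset.
- It also needs a stated exclusion restriction: allocation has no effect on outcome in never-starters. This should be discussed, because TAU children receive detailed referral information and the article describes none for KIDNET children who do not start.
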